## Reporting of adverse events

All adverse events (as outlined below) should be reported to the PI and CI. Depending on the nature of the event the reporting procedures below should be followed. Any questions concerning adverse event reporting should be directed to the Chief Investigator in the first instance.

### Non-serious Adverse Event (NSAE)

All such events, whether expected or not, should be recorded.

This is a case control study and doesn't include any clinical or experimental interventions other than blood sampling. In addition, natural history of DILI includes progressive worsening of the liver injury even after offending agent/ medication/ drug has been withdrawn. Acute liver failure and death are recognised complication. Therefore, while we will record accurately the severity of DILI formally based on the international consensus criteria [40].

### Serious AEs

An SAE form should be completed and faxed to the Chief Investigator within 24 hours. A Serious Adverse Event (SAE) is any adverse event occurring following study mandated procedures, having received the treatment or intervention that results in any of the following outcomes. However, acute liver failure, liver transplantation and death are recognised consequences of DILI and these will be recorded as part of the outcome of DILI as recommended by consensus criteria [40]. Therefore, following will NOT be considered as SAE:

1. Liver related death
2. Acute liver failure
3. Liver transplantation
4. Inpatient hospitalisation or prolongation of existing hospitalisation
5. A disability / incapacity

In the current study we will be performing venepunctures for blood sampling. So, we will report major bleeding leading to hypotension, drop in Hb, requirement of resuscitation, transfusion or hospital admission as adverse events. All SAEs should be reported to the North West - Haydock Research Ethics Committee where in the opinion of the Chief Investigator, the event was:

- 'related', ie resulted from the administration of any of the research procedures; and
- 'unexpected', ie an event that is not listed in the protocol as an expected occurrence

Reports of related and unexpected SAEs should be submitted within 15 days of the Chief Investigator becoming aware of the event, using the COREC SAE form for non-IMP studies.

Local investigators should report any SAEs as required by their Local Research Ethics Committee and/or Research & Development Office.

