## **ADVERSE EVENTS**

### **Definitions**

**An adverse event is any unfavourable and unintended sign, symptom, syndrome or illness that develops or worsens during the period of observation in the study.**

An AE does include a / an:

1. Exacerbation of a pre-existing illness.
2. Increase in frequency or intensity of a pre-existing episodic event or condition.
3. Continuous persistent disease or symptoms present at baseline that worsen following the start of the study.

A Serious Adverse Event (SAE) is any untoward and unexpected medical occurrence or effect that:

- Results in death
- Is life-threatening – refers to an event in which the subject was at risk of death at the time of the event; it does not refer to an event which hypothetically might have caused death if it were more severe
- Requires hospitalisation, or prolongation of existing inpatients' hospitalisation

Page 18 of 29

ChILI Protocol Final V1.6 / date 26/02/2024

|                                                                                                                                                                                                                                         |
|-----------------------------------------------------------------------------------------------------------------------------------------------------------------------------------------------------------------------------------------|
| This protocol is confidential and the property of the University of Nottingham. No part of it may be transmitted, reproduced, published, or used by other persons without prior written authorisation from the University of Nottingham |
|-----------------------------------------------------------------------------------------------------------------------------------------------------------------------------------------------------------------------------------------|

- Results in persistent or significant disability or incapacity
- Is a congenital anomaly or birth defect

Important medical events that may not result in death, be life-threatening, or require hospitalisation may be considered a serious adverse event when, based upon appropriate medical judgment, they may jeopardize the patient or participant and may require medical or surgical intervention to prevent one of the outcomes listed in this definition

AE doesn't include a/ an:

1. Exacerbation of a pre-existing illness or progression of underlying malignancy.

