2. Increase in frequency or intensity of a pre-existing episodic event or condition.
3. Condition detected or diagnosed after medicinal product administration even though it may have been present prior to the start of the study.
4. Continuous persistent disease or symptoms present at baseline that worsen following the start of the study.
5. Medical or surgical procedure (e.g., surgery, endoscopy, tooth extraction, transfusion); but the condition that lead to the procedure is an AE.
6. Pre-existing disease or conditions present or detected at the start of the study that did not worsen.
7. Situations where an untoward medical occurrence has not occurred (e.g., hospitalisations for cosmetic elective surgery, social and / or convenience admissions).
8. Disease or disorder being studied or sign or symptom associated with the disease or disorder unless more severe than expected for the participant's condition.
9. Overdose of concurrent medication without any signs or symptoms.

All adverse events will be assessed for seriousness and expectedness:

A distinction is drawn between serious and severe AEs. Severity is a measure of intensity whereas seriousness is defined using the criteria above. Hence, a severe AE need not necessarily be serious.

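### The safety section contradicts itself on when a bleed from research venepuncture is a serious adverse event, so such a bleed may miss the 24-hour SAE form and the 15-day ethics report

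*Protocol*

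**What the plan says.** The rules are split between two places in the Protocol.

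**Adverse Events, Definitions.** The general definition begins "A Serious Adverse Event (SAE) is any untoward and unexpected medical occurrence or effect that" and then lists death, life-threatening events, hospitalisation or its prolongation, lasting disability, and congenital anomaly. Important medical events may also count on medical judgement, where "they may jeopardize the patient or participant and may require medical or surgical intervention to prevent one of the outcomes listed in this definition". The section adds: "All adverse events will be assessed for seriousness and expectedness".

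**Reporting of adverse events.** All adverse events go to the PI and the Chief Investigator, with no time limit stated. The non-serious subsection says that the study has no intervention other than blood sampling.

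**Serious AEs.**
- The time limit: "An SAE form should be completed and faxed to the Chief Investigator within 24 hours".
- A second definition: an SAE "is any adverse event occurring following study mandated procedures, having received the treatment or intervention that results in any of the following outcomes". No list of qualifying outcomes follows. What follows is a list of five things that are not SAEs.
- Item 4 of that list is "Inpatient hospitalisation or prolongation of existing hospitalisation". Item 5 is disability or incapacity. Item 1 is restricted to liver-related death; items 4 and 5 carry no such restriction.
- On venepuncture: "we will report major bleeding leading to hypotension, drop in Hb, requirement of resuscitation, transfusion or hospital admission as adverse events".
- Reports go to the ethics committee within 15 days for SAEs that the Chief Investigator considers related and unexpected. Unexpected is explained as "ie an event that is not listed in the protocol as an expected occurrence".

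**The concern.** Bleeding is the event most likely to be attributable to the research itself. The consequences that the protocol attaches to it (hypotension, resuscitation, transfusion, admission) overlap its own seriousness criteria. Yet the sentence calls these bleeds adverse events, while the sentences around it speak of SAEs, and the neighbouring rules conflict on what an SAE is. Only SAEs trigger the 24-hour form, and only related and unexpected SAEs trigger the 15-day report.

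At stake is oversight rather than any estimate. The protocol allows enrolment of patients with encephalopathy who lack capacity, and justifies this partly by saying that the risk to them is negligible. A serious bleed caused by a research blood draw bears directly on that justification. Under the present text, two sites could classify the same bleed differently, and one of them might not send it for expedited review.

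**Working it through.** The main check is a reading of the two sections side by side; the protocol states no figure to reproduce.

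**Step 1: is the bleed serious?** Take each type of bleed in turn.

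| Bleed after research venepuncture | Definitions | Serious AEs exclusions | Result |
|---|---|---|---|
| Participant at risk of death, resuscitation needed | Serious (life-threatening) | Not excluded | SAE route open |
| Transfusion needed, not life-threatening | May be serious, as an important medical event on judgement | Not excluded | SAE route open, on judgement |
| Hypotension or fall in Hb alone | Serious only on the same judgement | Not excluded | SAE route open, on judgement |
| Serious only because it led to or prolonged admission | Serious (hospitalisation) | Excluded by item 4, whatever the cause | Direct contradiction |
| Serious only because it led to lasting disability | Serious (disability) | Excluded by item 5, whatever the cause | Direct contradiction |

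The admission row matters most, because hospital admission is one of the consequences named in the bleeding sentence itself. For the other rows, a site using only the Serious AEs section finds no positive criterion to apply, since the promised outcomes are missing.

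**Step 2: does expectedness remove SAE status?** The Definitions require an SAE to be unexpected. The definition under Serious AEs does not contain that word, and both sections elsewhere treat expectedness as a separate assessment. Under the first definition, a bleed judged expected is not an SAE at all, so the 24-hour form falls away as well as the ethics report. Under the second, only the ethics report is affected.

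**Step 3: is the bleed expected?** The test is whether the protocol lists it as an expected occurrence. The protocol has no list under that label. It names the bleed but does not call it expected. Either reading is possible.

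**Step 4: how often could this arise?** The documents give no bleeding rate, so only a range over assumed rates can be shown.
- Sampling visits, from the planned 40 cases with three visits and 120 controls with two: 40 × 3 + 120 × 2 = 360.
- Chance of at least one major bleed at rate p per visit: 1 − (1 − p)^360.
- Assumed p = 1 in 100,000: about 0.4%.
- Assumed p = 1 in 10,000: about 3.5%.
- Assumed p = 1 in 1,000: about 30%.

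The visit count is approximate. Cases arising in the CPI cohort have a fourth visit, which raises it. Research bloods are to be taken with clinical bloods as far as possible, so many visits add no separate needle puncture. The range is too wide to support any single figure.

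**The case against.** A reader might infer that the protocol downgrades these bleeds to non-serious, that they can never trigger expedited reporting, and that naming them makes them expected. The documents do not support this, for several reasons.

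- The bleeding sentence stands under Serious AEs, after the exclusions and directly before the rule on reporting SAEs to the ethics committee. It can be read as naming what remains reportable.
- The second definition makes SAEs a subset of adverse events, so calling a bleed an adverse event does not make it non-serious.
- Every adverse event must be assessed for seriousness. The life-threatening and important-medical-event routes are not among the five exclusions.
- Nothing labels bleeding as expected. The language of recognised consequences is applied to acute liver failure, transplantation and death.
- All adverse events reach the PI and the Chief Investigator, and local investigators must report SAEs as their local committee or R&D office requires.
- Relatedness is missing from the assessment sentence in the Definitions, but the Chief Investigator assesses it under Serious AEs. That omission is editorial.

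All of this stands, and it limits the conclusion to what may happen. It does not remove the contradiction over admission. The exclusions are introduced by a reference to consequences of DILI, so items 4 and 5 were probably meant to cover only such consequences. But item 1 states its restriction to liver-related events and items 4 and 5 do not. Nor does the general reporting route replace the time limits, because it has none.

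**Conclusion.** The Definitions and the Serious AEs section contradict each other on when a research-caused bleed is a serious adverse event. The firmest conflict is hospitalisation: a seriousness criterion in one section and excluded without limit in the other. The missing outcome list, the two different SAE definitions and the open question of expectedness add to it. A serious bleed from research venepuncture may therefore escape the 24-hour form and the 15-day ethics report. It need not, because a site can also reach the SAE route from the same text.

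This conclusion rests on reading the rules as written and assumes no event rate. Such bleeds may well be very rare, but the documents do not allow that to be quantified. The point is minor: it concerns safety-reporting wording and affects no study estimate.

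**What to change.** Reconcile the two sections with three wording changes.

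1. In the Definitions, delete the requirement that an SAE be unexpected, so that expectedness is judged separately and only for the ethics report.
2. Under Serious AEs, replace the reference to outcomes that are not listed with a reference to the seriousness criteria in the Definitions. Limit exclusion items 4 and 5 to hospitalisation and disability that result from the liver injury or underlying disease, so that they do not cover consequences of research procedures.
3. Reword the bleeding sentence along these lines: major bleeding after research venepuncture that meets any seriousness criterion in the Definitions is reported as an SAE and is not a listed expected occurrence; the Chief Investigator assesses relatedness case by case.

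The second change must accompany the third. If item 4 stayed as it is, the new sentence would conflict with it for bleeds leading to admission. Adding relatedness to the assessment sentence in the Definitions would be a useful tidy-up but is not essential.

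The cost is a short text amendment and possibly a very few extra SAE forms. Design, sample size and analysis are unchanged.

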## **TRANSPORT AND STORAGE OF THE TISSUES**

Samples collected prospectively will be stored in a linked anonymised format and labelled using a combination of study reference, unique study identifier and cross referenced with location code numbers to permit accurate linkage to study data and the consent form. Liver tissue from patients with AIH and DILI collected from the archive of the histology department at Nottingham University Hospitals NHS Trust will be fully anonymised FFPE preserved samples from the archive will be returned or disposed.

Samples for NHS pathology analysis will be labelled in accordance with local NHS procedures.

Serum, plasma, whole blood, tissue, purified cells (PBMCs), urine, and stool samples will be stored in aliquots at -80°C in the Nottingham Digestive Diseases Centre within University of Nottingham, in the Queens Medical Centre Campus, held under HTA licenced premises (Designated Individual: [name], Licence Number 12265). When the study closes, samples will be transferred to NDDC BRU research tissue bank. Samples will be shipped following HTA and International laws with appropriate agreements in place. Samples including liver tissue may be sent to our partners, Pfizer in USA and specialist analytical centres worldwide (contract in place).

The master database will be held by the CI and designated individuals in a password encrypted file.

Where participants do not agree to the future use of the samples they will be destroyed in accordance with the Human Tissue Act, 2004.

## LABORATORY ANALYSES

Each participating NHS hospital site will carry out all routine laboratory analysis as part of normal patient care. Blood will be processed in Nottingham Digestive Diseases Centre or Nottingham BRC lab for storage of serum and plasma as outlined in the SOP. Data and all appropriate documentation will be stored for a minimum of 25 years after the completion of the study, including the follow-up period.

We will collate detailed and comprehensive clinical and demographic data using electronic case report form (CRF) on the University of Nottingham REDCap platform. Data from analysis of biological samples (i.e. biomarkers) and histology will be collated and linked to clinical characteristics on study databases to achieve in-depth phenotyping.

## STATISTICS

### Statistical analysis

- We will calculate the incidence of ChILI and other irAE in the cohort group.
- We will describe demographic and clinical data for the enrolled participants using descriptive statistics, mean  $\pm$  standard deviation (SD) for continuous measurements and frequencies and percentiles for categorical data. We will compare patients' pathological and clinical characteristics using Chi-square test for categorical variables and Wilcoxon/Kruskal-Wallis test for the continuous variables.  $P < 0.05$  will be considered statistically significant.
- We will assess the accuracy of the biomarkers for ChILI detection and predicting prognosis using receiver operating characteristic (ROC) curve and the area under the ROC curve (AUC) with 95% confidence interval (CI).
- We will assess the correlation of biomarkers with ALT using Pearson's  $r$  coefficient.

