### Hypothesis:

We hypothesise that checkpoint inhibitor-induced liver injury (ChILI) is determined by factors that modulate cellular and immunological response to the development of ChILI and can be recognised by a combination of markers.

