## **STUDY MANAGEMENT**

Participants enrolled prospectively will be asked to give consent for their samples to be collected, stored and used for the purposes of this study. Clinical and phenotypic data will be collected.

Blood collected will be used for genetic analyses of genetic variants (not genetic testing for clinical genetic disease diagnostics) and for immune cell characterisation. The total volume of blood taken for these samples will not exceed 80ml.

We propose to prepare peripheral blood mononuclear cells (PBMCs) for phenotypic analysis such as scRNAseq and immunological cell-type analyses. Plasma and serum will be prepared from blood samples after collection and analysed or stored at -80°C for subsequent analysis of biomarkers, metabolites and other cellular components. We plan assessment of proposed circulating biomarkers including cytokines, microRNAs (miR-122, miR-4270 and miR-4463)[39], total cytokeratin 18 (K18), macrophage colony-stimulating factor receptor (MCSFR) [11], and any others identified in subsequent publications. Some of these molecules may be quantified by specialist laboratories via service agreements. Urine

biomarkers and metabolites will be evaluated and metabolites and microbiome assessed from stool samples.

We will also collect liver biopsy material surplus from clinical care where available only if taken as part of usual patient treatments for their condition. We plan to use **available** liver biopsies, up to 25 of DILI and 50 of AIH, from other HRA-approved research studies, tissue banks and the histopathology archive at NUHT to examine the cellular features of disease and provide phenotypic details of changes within liver tissues that accompany the disease development.

We will also request consent for any residual samples after the study is complete to be transferred to a research tissue bank or stored under the University HTA license and used for future research by other researchers.

In this case, samples will be stored at the NDDC BRU Research Tissue bank (REC. Ref: 19/WA/0288; IRAS 269956) and made available through the access committee. The Chief Investigator has overall responsibility for the study and shall oversee all study management.

The data custodian will be the Chief Investigator. Anonymised data will be shared with researchers at Pfizer where appropriate for analysis of research findings.

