#### Sample size and justification

This is a mechanistic study to document the disease natural history rather than evaluate performance of specific biomarkers. As this uses specialist methods, we will only be able to recruit from a small number of suitable sites near to analytical facilities so sample size is limited by availability of suitable participants. Due to rarity of checkpoint inhibitors induced liver injury, incidence rate are between 3-18 % of patients receiving CPI, we aim to enrol 40 cases and 120 controls who received CPI without developing liver injury over 3 years. This is feasible at this centre based on current records of CPI treatment.

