### Primary Outcome Measure

1. To estimate the incidence of checkpoint inhibitor-induced liver injury (ChILI) and other immune-mediated adverse reactions.
2. To identify and characterise biomarkers associated with the diagnosis of ChILI

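### Plain AUCs with 95% CIs are over-optimistic for any marker or combination chosen in the same 160 patients, and the protocol contradicts itself on whether biomarker performance is evaluated

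*Protocol*

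**What the plan says.** All references are to the protocol.

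- **Primary Outcome Measure**, item 2: "To identify and characterise biomarkers associated with the diagnosis of ChILI".
- **Hypothesis**: ChILI "can be recognised by a combination of markers".
- **Study Management**: the circulating candidates are cytokines as a class, three named microRNAs (miR-122, miR-4270, miR-4463), K18 and MCSFR, "and any others identified in subsequent publications". The same section plans genetic variants, single-cell RNA sequencing and immune cell typing, urine biomarkers and metabolites, and stool metabolites and microbiome. No number of markers is given.
- **Statistical analysis**, second bullet: "We will compare patients' pathological and clinical characteristics using Chi-square test for categorical variables and Wilcoxon/Kruskal-Wallis test for the continuous variables". This bullet ends with the rule that P<0.05 "will be considered statistically significant", the only threshold in the document.
- **Statistical analysis**, third bullet: "We will assess the accuracy of the biomarkers for ChILI detection and predicting prognosis using receiver operating characteristic (ROC) curve" and its AUC with a 95% confidence interval. A fourth bullet correlates biomarkers with ALT. Neither bullet has a threshold, a selection step or a validation step.
- **Sample size and justification**: 40 cases and 120 controls, set on feasibility, because the study is mechanistic "rather than evaluate performance of specific biomarkers".

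**The concern.** An AUC and its usual confidence interval are valid for a marker fixed before the data are seen. They are not valid for a marker picked because it did well in those data, or for a score whose weights were fitted to them. Here a primary outcome is to identify markers from an open list, the hypothesis is about a combination, and the 40 cases and 120 controls are the only comparison set the protocol provides. Identification and accuracy would therefore come from the same patients.

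If so, a study with no true marker could still report one with an interval that excludes 0.5, and a combination that looks clinically useful. Neither would replicate.

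The sample size section makes this worse. It gives the absence of a performance evaluation as part of the reason why no precision or power target is set, yet the statistics section plans accuracy for both detection and prognosis.

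**Working it through.** **Inputs from the protocol.** Cases 40, controls 120, total 160. Threshold 0.05 (sidedness not stated; two-sided assumed). Five individually named markers. The sample size comes with no power, effect size or target AUC, so there is no planning figure to reproduce.

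**Assumptions.** The number of markers *m* is not given; 5 is the individually named set, and 20, 100 and 1,000 illustrate a longer list. All markers are taken as null and independent. Correlation would lower the chance of any false positive but not the expected number.

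**Step 1. False positives if 0.05 were used for each marker.** Expected number = 0.05 × m; chance of at least one = 1 − 0.95^m.

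| m | Expected | At least one |
|---|---|---|
| 5 | 0.25 | 1 − 0.95^5 = 22.6% |
| 20 | 1 | 1 − 0.95^20 = 64.2% |
| 100 | 5 | 1 − 0.95^100 = 99.4% |
| 1,000 | 50 | about 100% |

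**Step 2. Apparent AUC after selection.** Independent standard normal null markers were simulated in 40 v 120 (400 runs; 150 for m = 1,000). Each run took the best single AUC in either direction with its naive 95% CI, then a Fisher linear combination of the top five, scored in the same data and in fresh data.

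| m | Best single marker, mean AUC | Naive CI excludes 0.5 | Top-5 combination, same data | Top-5 combination, new data |
|---|---|---|---|---|
| 5 | 0.58 | 19% | 0.61 | 0.50 |
| 20 | 0.61 | 63% | 0.68 | 0.50 |
| 100 | 0.65 | 98% | 0.75 | 0.50 |
| 1,000 | 0.68 | 100% | 0.82 | 0.50 |

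Fitting weights is enough to cause the problem, even without selection. A linear score using all of 5, 10 or 20 null markers has a mean apparent AUC of 0.61, 0.66 or 0.73. For five markers its naive CI excludes 0.5 in just over half of runs.

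**Step 3. Precision of an AUC at this sample size (Hanley-McNeil).** SE² = [A(1 − A) + (n1 − 1)(Q1 − A²) + (n2 − 1)(Q2 − A²)] / (n1·n2), with Q1 = A/(2 − A) and Q2 = 2A²/(1 + A). At A = 0.8, n1 = 40, n2 = 120:

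- Q1 = 0.6667 and Q2 = 0.7111.
- SE² = (0.16 + 39 × 0.0267 + 119 × 0.0711)/4800 = 0.00201, so SE = 0.045.
- Half-width = 1.96 × 0.045 = 0.088, an interval of about 0.71 to 0.89.

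At A = 0.7 the interval is about 0.60 to 0.80.

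**Step 4. Cost of correction.** Bonferroni is used as a conservative bound; false discovery control would usually cost less. The difference detectable with 80% power is (z for α/2 + z for 0.80) × √(1/40 + 1/120). At α = 0.05 this is (1.960 + 0.842) × 0.1826 = 0.51 SD. It rises to 0.71 SD for 20 markers (α = 0.0025) and 0.79 SD for 100 (α = 0.0005). Power for a true 0.6 SD difference falls from 91% to 60% and 42%.

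**Step 5. The two sections side by side.** The sample size section says that evaluating the performance of specific biomarkers is not the aim. The statistical analysis section says biomarker accuracy will be assessed by ROC curve and AUC. Accuracy by ROC is performance, so both cannot stand as written.

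**The case against.** The strongest reply is that the protocol does not state the faulty analysis. Four parts of that reply stand.

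- **The threshold.** A reader might infer that P<0.05 is the declared rule for the omics search. The sentence closes the bullet on clinical and pathological characteristics, and the biomarker bullets carry no threshold. Step 1 therefore shows what would follow if the only available threshold were borrowed, not what the protocol prescribes.
- **The combination.** A reader might infer that a multivariable score is planned. The statistics section contains none; the idea comes from the hypothesis.
- **The counts.** Only five markers are individually named, and for those the false-positive risk is modest. Larger counts are assumptions. Later-published candidates would be nominated by outside literature, and nothing says that every transcript or metabolite will be given an AUC.
- **The unseen SAP.** Selection and validation methods commonly sit in a SAP, which may exist. Their absence here does not show that the final analysis will be uncorrected.

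The reply does not remove the point. The protocol does fix the biomarker method as a plain AUC with CI, does make identification a primary outcome, and does leave the list open with no second data set. The optimism in Step 2 needs no P-value threshold and arises with single markers. The conflict between the two sections lies in the protocol's own text, so a SAP cannot settle it.

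**Conclusion.** The point holds in a limited form. As written, the plain AUC and 95% CI are suitable for a prespecified single marker, but would be over-optimistic for any marker or combination selected or fitted in these 160 patients. Under independent null markers, the excess over 0.50 is about 0.11 for the best of 20, 0.15 for the best of 100 and 0.25 for the top-5-of-100 combination. The last two of these AUCs (0.65 and 0.75) also exceed 0.50 by more than the nominal half-width of about 0.10 to 0.11 for a true AUC of 0.5 to 0.7 at this sample size, so the interval gives no protection.

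These sizes rest on assumed marker counts, independence, and reaching 40 cases and 120 controls. The documents do not support the stronger statement that the study will declare false biomarkers: no rule for declaring screened markers is stated, and an unseen SAP may supply one. The contradiction over whether biomarker performance is evaluated depends on none of these assumptions. The change should be made, because a primary outcome is affected and the remedy is cheap.

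**What to change.** In the statistical analysis section:

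1. Limit unadjusted P<0.05 to clinical and pathological characteristics and to the five individually named markers (miR-122, miR-4270, miR-4463, K18, MCSFR).
2. Declare all other screened markers, including cytokines, later-published markers and omics features, by Benjamini-Hochberg false discovery rate. Cytokines and later additions belong here because they are an unspecified class and an open list.
3. Report the AUC of any selected or combined marker as optimism-corrected, by bootstrap or cross-validation that repeats the selection and fitting steps in each resample. This includes a fitted combination of the five named markers.
4. Reconcile the sample size section with the statistics section by stating that biomarker AUCs are exploratory, with a 95% CI half-width of about 0.09 at a true AUC of 0.8.

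The cost is wording and analysis time; no extra patients, samples or visits are needed. Fewer markers will be declared, reported AUCs will be lower, and screened markers lose some power, bounded by the Bonferroni figures in Step 4.
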